**Longitudinal design.**

### Randomization

The randomization comprises on the one hand the randomization to one of the four groups (two control groups and two intervention groups) and on the other hand the gender-balanced randomization of the couple into a target person receiving the intervention and a partner condition. For this reason, blocking as means of restricted randomization is used. Within a block of eight participating couples, two couples each are assigned to one of the four groups, once the man and once the woman assigned as target person. Before the beginning of the study, a computerized random-number generator is used for sequence generation of blocks. This allocation sequence is generated by an assistant that is not part of the study team and concealed in a set of sealed, numbered envelopes, and thus remain unknown to any of the investigators until the group assignment. On the day of the baseline assessement (T1), the interviewer conducting the session opens the appropriate numbered envelope and prepares the study materials accordingly.

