### Power analysis

Effect sizes of action control interventions are medium to large (e.g., *f*^2^ = .25 in the study of Scholz & Sniehotta [46]; *f*^2^ = .42 in the study of Schüz et al. [23], for the volitional group). Thus, the analyses for the intervention effects from baseline to the two follow-ups with an assumed small correlation among repeated measures of *r* = .2 due to the expected change across time, with a power of .80, an alpha level of .05, a medium effect size of *f*^2^ = .25, and four intervention groups requires a total sample size of *N* = 88 couples (analyses are powered for between-effects on the individual; G*Power Version 3.1.9.2, [47]). Although there is one study reporting an attrition rate of 52% after 6 months for participants of a weight loss intervention [48], many intervention trials targeting physical activity report attrition rates around 20% [50, 51] across 6 months to two years. Thus, we conservatively assume an attrition rate of 30%. This results in *N* = 116 (*n* = 29 per group) couples needed for appropriate powered analyses of the effect of the intervention across the three points of measurement.

For the analyses on the intraindividual level during the diary phase, it is not possible to run power analyses. This is due to the fact that these power calculations require detailed information on parameters from previous studies [49]. Because this study is the first to test effects of individual and dyadic action control on daily physical activity, this kind of power analysis cannot be reported. Therefore, this study will serve as a basis for future studies focusing on intraindividual associations of dyadic and individual action control interventions.

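### The 116 couples do not preserve the required 88 at the assumed 30% attrition: about 81 remain, and 88 survive only if attrition is at most about 24%

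*Protocol article*

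**What the plan says.** All the figures stand in the Power analysis section of the protocol article. The comparison of four groups from baseline to the two follow-ups is powered "with a power of .80, an alpha level of .05", "a medium effect size of *f*^2^ = .25" and a "small correlation among repeated measures of *r* = .2". The calculation is for between-person effects. With these inputs the analysis "requires a total sample size of *N* = 88 couples".

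The section then reviews attrition. One weight-loss study lost 52% by six months, while many physical activity trials lost around 20%. It settles on 30% and calls this conservative: "we conservatively assume an attrition rate of 30%. This results in *N* = 116 (*n* = 29 per group) couples needed". That number is said to power the analysis of the intervention effect adequately "across the three points of measurement". The inflation formula is not printed, and nothing elsewhere in the article gives another attrition rate for this trial or another reason for 116.

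**The concern.** The text presents 116 as the consequence of 88 and 30%. An attrition rate is a fraction of those randomised, so the required number has to be divided by the fraction retained. Multiplying by one plus the rate gives too small a number, and the gap widens as the rate rises. The 116 looks like the result of multiplying.

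At stake is the trial's headline sample size. A reader will take it that 116 couples can lose 30% and still meet the stated requirement, and will judge the adequacy of the trial on that basis. If the margin fails at the very rate assumed, the protection described as conservative is not there.

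**Working it through.** **Inputs** (Power analysis section unless noted): alpha 0.05; power 0.80; k = 4 groups; m = 3 measurements; correlation ρ = 0.2; effect size printed as f² = .25; required N = 88; attrition 30%; stated N = 116, 29 per group. Equal allocation comes from the Randomization section.

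**1. Reproduce the 88.** For the between factor of a repeated measures ANOVA, use the noncentral F with k − 1 and N − k degrees of freedom and noncentrality λ = f² × N × m / (1 + (m − 1)ρ).

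- Reading the effect size as f = .25 (f² = .0625): the smallest N with power of at least 0.80 is 86 (λ = 0.0625 × 86 × 3 / 1.4 = 11.52, power 0.803). Rounded up to equal groups this is 88 (λ = 11.79, power 0.814), which matches the plan.
- Reading it as printed (f² = .25): the smallest N is 25, or 28 in equal groups. This does not match.

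The 88 therefore rests on f = .25, and the power figures below assume that reading.

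**2. Reproduce the 116.**

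- Multiplying: 88/4 = 22 per group; 22 × 1.3 = 28.6, rounded up to 29; 29 × 4 = 116. Exact match.
- Dividing: 88/0.70 = 125.7, so 126. By group, 22/0.70 = 31.4, rounded up to 32; 32 × 4 = 128. No match.

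**3. What 116 delivers.**

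- Remaining at 30% attrition: 116 × 0.70 = 81.2, about 81, which is 88 − 81 = 7 short.
- Attrition at which 88 remain: 1 − 88/116 = 24.1%.
- Attrition at which 86 remain, the minimum for 80% power: 1 − 86/116 = 25.9%.

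**4. Power under f = .25.**

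| Couples analysed | Power |
|---|---|
| 88 | 0.814 |
| 86 | 0.803 |
| 81 | 0.775 |

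**5. What 30% attrition would need.**

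- To retain the stated 88: 126 couples (128 in equal groups), that is 10 to 12 more than 116.
- To hold 80% power only (86 completers): 86/0.70 = 122.9, so 123 (124 in equal groups), that is 7 to 8 more.

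**The case against.** The best defence is that little hangs on it. Power slips by about 2.5 points from the stated 0.80. At around 20% attrition, the rate the section reports for many physical activity trials, 116 × 0.80 = 92.8 couples remain, more than the requirement. The Discussion stresses how hard couples are to recruit and recommends emphasis on effect sizes over significance tests. All of this stands and bears on severity. It does not make the sentence true, because the plan chose 30% and derived 116 from it.

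It can also be said that multiplication is only inferred, since no formula is printed. That is so, but the mismatch between 88, 30% and 116 does not depend on how it arose. Couples lost before the last follow-up might still contribute data, but the planned analysis across three time points is a repeated measures ANOVA in SPSS, which ordinarily uses complete cases, so partial data do not obviously rescue the figure.

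The effect-size notation cuts the other way. Taken literally, f² = .25 gives power above 0.999 at 81 couples. But then the 88 itself is unexplained, so the literal reading moves the inconsistency without removing it.

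Stronger readings are tempting and are not supported:

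- A reader might infer that 80% power at 30% attrition demands 126 couples. It does not: 86 completers suffice, hence 123 or 124. The 126 is what retaining the stated 88 requires.
- A reader might measure the error by the 52% attrition rate. The section cites that rate from one study and does not adopt it.
- A reader might object that 116 is not a multiple of the block of eight. The Randomization section does not promise exact final balance, and ending within a block is ordinary and unrelated to the attrition arithmetic.

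**Conclusion.** The figure is wrong as written. On the plan's own 88 and 30%, 116 couples are too few: about 81 remain, and the requirement of 88 is met only up to about 24% attrition. This conclusion needs no assumption about the effect size.

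The power consequence does. It rests on reading the printed f² = .25 as f = .25, on three measurements with ρ = 0.2, and on analysis of completers. On that basis power at 30% attrition is about 0.775, slightly under the stated 0.80, and 80% power is kept up to about 26% attrition. A reader might infer that the trial is seriously underpowered or must recruit more couples; a shortfall of this size supports neither. It is a should-fix correction to a stated number, with no change to design or analysis.

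**What to change.** Replace the sentence on the inflated sample size with wording such as: *N = 116 randomised couples leaves about 81 completers at 30% attrition (power about 0.77 with f = .25); 88 completers are reached only if attrition is at most 24%.*

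In the same edit, have the sponsor confirm which effect-size quantity was entered in the calculation and correct the notation so that it agrees with N = 88.

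The cost is one restated sentence, one corrected symbol and a slightly less favourable power statement. No extra couples are needed. If the sponsor prefers to keep the statement that 88 couples are retained at 30% attrition, the number that goes with it is 126 (128 in equal groups).

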### Ethics

This study was approved by the institutional review board of the Faculty of Human Sciences of the University of Bern, 21 February 2012 (Reference number: 2011-12-36206).

## Discussion

Regular physical activity in accordance to the recommendations of the WHO can have important health benefits, especially in overweight and obese individuals. Changing one’s habitual physical inactivity, however, is a difficult endeavor. Common health behavior change theories focus almost exclusively on individual self-regulation. At the same time, there is research on social exchange processes (i.e., social support, social control) that demonstrate the importance of social network members with regard to health behavior change e.g., [32, 33]. One promising way to integrate social influence into the standard health behavior change approach is the dyadic conceptualization of individual regulation variables. For example, this has been done with implementation intentions e.g., [34, 35]. This study aims at targeting action control on a dyadic level by including couples and testing whether a partner-based dyadic action control intervention is more effective than an individual action control intervention compared with no-intervention control groups. The study uses an ecological momentary intervention [42] and combines macro- and micro-time assessments [38] in order to not only focus on longer-term effects of the intervention, but also to examine immediate intervention effects on a daily basis.

There were several issues that arose during the development of the study protocol and subsequently during the recruitment process and the implementation of the study. Regarding the study protocol and the planning of the intervention, one critical point is that the intervention comprises several components and that the two intervention groups are not merely different with regard to the ecological momentary intervention (i.e., the text message-based dyadic or individual action control intervention). Instead, the setting of the behavioral intentions also differs between the two groups in that target persons of the dyadic group form these intentions in collaboration with their partners and target persons of the individual group form these intentions alone. There were several reasons speaking in favor for this procedure. First, the dyadic action control intervention made it necessary to include partners into the goal setting process in order to have no logical problem when partners are sending text messages to the target persons regarding the intended increase in physical activity. Moreover, including the partners in the goal setting process might also increase the partners’ commitment to comply with the intervention protocol. Including the partners of the individual action control group also in the goal setting process, however, endangered introducing too much social influence into this group. Thus, the individual group participants completed the goal setting task on their own. Future studies might want to disentangle effects of joint goal setting and the text messages. For example, by including another experimental group that only engages in goal setting but does not receive text messages with action control content.

Another challenge was the decision as to whether providing smartphones to the participants or to let them use their own smartphones. The downside of the decision to provide smartphones to participating couples is that this might introduce quite an artificial component into the ecological momentary intervention design. For example, it is less natural to receive a text message from one’s partner on a smartphone provided by study personnel than on one’s own smartphone. However, there were several reasons why we decided in favor of providing smartphones. First, we did not want to exclude anyone who does not have an own smartphone. And second, with providing smartphones, we are able to control the intervention fidelity in terms of controlling if and when partners send the messages they were supposed to send to the target persons and if and when target persons received the text messages.

Finally, there is a trade-off between conducting a state-of-the-art ambulatory momentary assessment of physical activity and its antecedents by self-report and the danger of confounding effects of the ambulatory momentary assessment with the action control intervention. Instructing individuals to report all incidents of moderate-intensity physical activity over 10 minutes using the smartphones is likely to also trigger self-monitoring. Thus, the compromise we chose for this study was an objective ambulatory momentary monitoring by instructing participants to use accelerometers and assess the self-reported physical activity only once a day (in the hour before going to bed) in order to lower the impact of the diary method on our target variable action control. Moreover, in order to control for the effect of the diary on physical activity, we introduced control group II that has objective assessment of physical activity only, but no self-report in order to control for the potential effects of the self-reporting physical activity.

Another important point regarding the present study concerns the successful recruitment of couples meeting all the inclusion and none of the exclusion criteria and who are willing to partake in this intensive design. When it comes to couple studies, the first problem is that it always needs the consent of both partners to participate, which makes it much more difficult to find participants. When there are additionally relatively strict inclusion and exclusion criteria as is the case in the present study, the recruitment process can be very challenging. This needs to be kept in mind when evaluating the sample size of couple studies. In line with common standards we therefore recommend to abandon the strong focus on significance testing and to focus on effect sizes instead.

Despite these challenges outlined above in conducting studies with couples and applying ecological momentary interventions, we are convinced that this study will substantially further our knowledge with regard to social influences in health behavior change.

## Endnote

^a^One popular model of behavior change that explicitly integrates social support is the Transtheoretical Model of Behavior Change (TTM) [30]. In the TTM one of ten processes of change is “helping relationships” [30]. Helping relationships are defined as the support of others during behavioral change and is operationalized as a measure of *perceived* social support. Moreover, in the TPB [7] subjective norms are included as one predictor of intentions. Subjective norms, however, are defined as the subjective perception of expectations significant others have on the target person to change his/her behavior. Thus, social network partners are not explicitly integrated in the TPB.
